## Abstract

**Background:**

Child sexual abuse (CSA) is a significant public health concern, and there is a lack of universal, evidence-based primary prevention interventions that extend beyond a focus solely on children. Parents remain a consistently underutilized target for primary prevention efforts aimed at mitigating CSA despite their unique relationship and close proximity to their children. CSA risk is not confined to any specific demographic, and its effects on affected children are well-documented, significantly impacting numerous dimensions of their wellbeing. Thus, there is a clear and urgent need to address this gap in prevention strategies.

**Methods:**

This study will use a quasi-experimental design (target *N* = 412) to examine potential gains in CSA-related awareness and intentions to use protective behaviors among parents who participate in a universal parent-focused CSA prevention workshop, *Smarter Parents*. *Safer Kids*., compared to those who do not. Participants in both the control (*n* = 206) and experimental group (*n* = 206) will complete 3 survey assessments: Survey 0 (baseline), Survey 1 (1-month), and Survey 2 (3-month follow-up). The experimental group will participate in a *Smarter Parents*. *Safer Kids*. workshop between the Surveys 0 and 1. We will use data collected from the baseline to measure potential mediators of CSA-related awareness and intention to use protective and preventive behaviors. In adjacent efforts to enhance the curriculum’s reach with future dissemination and implementation, we will also explore the impact of recruitment materials and strategies on parental engagement.

**Conclusion:**

Results of this study will advance efforts to implement parent-focused CSA prevention with a universal audience.

## 1. Introduction

### 1.1. Background and rationale

Child sexual abuse (CSA) is an urgent public health concern estimated to impact over 60,000 children each year in the United States [1, 2]. It is widely accepted, however, that this is a gross underestimate of the true prevalence of CSA due to barriers in disclosure by children (e.g., the vocabulary required to disclose; an understanding of the acts that took place; access to supportive resources and trusted personnel; and fear of retribution, removal from the home, not being believed, social stigma and/or shame) [3, 4]. Evidence of this underrepresentation is displayed in the most recent report by the National Children’s Alliance indicating that while not all culminated in disclosure, 236,601 cases of CSA were opened and investigated by U.S. child advocacy centers in 2023 [5]. Consequences of CSA include lifelong adverse physical, psychological, social and behavioral health outcomes as well as an increased risk of subsequent revictimization [6], resulting in an estimated lifetime economic burden in excess of $9.3 billion USD for 1-year of substantiated victims [7]. Given the considerable magnitude of CSA and recognizing that CSA is a preventable issue [8], an increase in primary universal prevention efforts is urgently needed.

For years, CSA interventions adopted secondary and tertiary prevention approaches [9]–with a focus on streamlining efforts towards mitigating adverse outcomes of CSA after it has occurred and preventing revictimization. While important, this leaves a gap in preventing CSA from occurring in the first place–known as primary prevention [9–11]. The majority of extant evidence-based CSA primary prevention programs are largely child-focused and delivered in schools [12–14]. However, the field agrees that children should not bear the responsibility of protecting themselves from victimization. Parents (or primary caregivers) have long been neglected in primary prevention efforts for CSA [15], an indication of the unique etiology in comparison to other forms of maltreatment and the knowledge that parents are not often the primary perpetrators (36%) [16]. Parents are in an optimal position to communicate with and protect their children from harm, given both their unique physical proximity (i.e., monitoring) and the inherent nature of a parent-child relationship (i.e., communication, scaffolding of social norms) [10]. In a systematic review of 24 parent-focused CSA prevention programs, few studies (n = 7) used a randomized controlled trial design indicating a need in the evidence-base of these programs [17]. Improvement was most commonly observed related to parental behavioral intentions and response efficacy indicating a need to focus more on actual use of protective behaviors. Importantly, the review included no universal parent-focused CSA prevention efforts.

### 1.2. Parent-focused CSA prevention

Our team previously developed a parent-focused CSA prevention curriculum, *Smart Parents–Safe and Healthy Kids* [18, 19], which was designed to be an added session to parent-support programs. In this way, the curriculum adopted a selective approach to prevention [20] as children of parents enrolled in parent-support programs (e.g., home visitation programs) are seen to be at a heightened risk for CSA [21–23]. However, CSA affects children across all sexes, ages, races, ethnicities, and socioeconomic stratum. Therefore, a need remains for an evidence-based universal parent-focused CSA prevention curriculum.

Adapted from the selective intervention [19], we created *Smarter Parents*. *Safer Kids*. (hereafter *Smarter Parents*) to be a universal parent-focused CSA prevention curriculum which is delivered in a two-hour, single session group-based workshop for parents of children under 13-years old [24]. Beyond the age of 13, there enters a different level of complexity when adding in other levels of sexual behavior (e.g., dating) that arise after the onset of puberty. Thus, the curriculum maintains a focus on children under 13 –addressing the age group most vulnerable to CSA [25, 26]. As in the selective intervention, the universal *Smarter Parents* curriculum is behaviorally based and provides parents with developmentally appropriate information on three sections related to reducing risk for CSA: (a) healthy child sexual development; (b) parent-child communication about sex, sexual development, and sexual abuse; and (c) child safety (e.g., vetting babysitters, monitoring activities inside/outside the home and online). In the workshop, facilitators use structured discussions and interactive role-playing scenarios to practice the skills and strategies taught (i.e., “Your 3-year-old son saw your 4-year-old daughter naked after taking a bath. He says, ‘Where is sister’s wee-wee?’ How would you respond?”).

The *Smarter Parents* curriculum was pilot tested using a mixed methods approach to examine acceptability and feasibility [24]. Parent participants (*N* = 31) attended a workshop and completed pre- and postworkshop assessments measuring CSA knowledge and intention to use protective behaviors. Participants also engaged in a brief structured interview with the research team after the workshop. Mean post-workshop assessment scores increased meaningfully from pre-workshop assessment, and qualitative data indicated high acceptability. The pilot was limited by its small and homogeneous sample along with its lack of a control group [27]; however, results indicate promise for evaluating the effectiveness of the *Smarter Parents* curriculum in future research.

### 1.3. Current study

Next in the line of research to establish an evidence base for *Smarter Parents*, the current study will capitalize on the active implementation of *Smarter Parents* by nine community-based partners across the Commonwealth of Pennsylvania–referred to as Project Safe and Smart. This study will therefore use a quasi-experimental design (target *N* = 412) to examine potential gains in CSA-related awareness (i.e., knowledge of and attitudes toward appropriate CSA prevention strategies) and intentions to use protective behaviors among parents who participate in *Smarter Parents* compared to those who do not (Aim 1). Then, we will consider potential mediators of CSA-related awareness and protective behaviors (e.g., demographic characteristics, initial parenting strategies, use of protective and preventive behaviors; Aim 2). Lastly, we will also explore the impact of recruitment materials and strategies on parental engagement (i.e., workshop registration and attendance; Aim 3). Results of this study will contribute to the growing evidence base of *Smarter Parents* and will advance efforts to implement universal CSA prevention with parents and primary caregivers.

## 2. Methods

### 2.1. Workshop implementation

Implementation of the workshop by the nine community-based organizations is supported by grants awarded by a Pennsylvania state-government agency. Selected via competitive application process the sites represent victims service agencies, child advocacy centers, and youth serving organizations. Facilitators (*n* = 2 per site) were trained to deliver the *Smarter Parents* workshop in August of 2023. Once certified, facilitators could train other facilitators at their site to deliver the workshop; certification for all facilitators was provided by the research team. Implementation began in earnest across all sites in early 2024.

As designed, the group-based *Smarter Parents* workshop may be delivered in-person (i.e., at the site, a library, or other community location) or online (via interactive videoconferencing software such as Zoom). To achieve model fidelity, it is required each workshop follow a 1:10 ratio wherein there is 1 facilitator for every 10 participants (max. 20 participants). Parent participants will receive a physical copy of the *Smarter Parents* Parent Handbook at in-person workshops, or an electronic copy (i.e., PDF sent via email) for online workshops. Facilitators will submit an implementation form for each scheduled workshop regardless of the number of registrants or participants. This form documents the date and time of the workshop, number of registrants, number of participants, aspects of fidelity, rating of participant engagement, and documentation of any unforeseen circumstances (e.g., disclosure, interruption, etc.). Facilitators are encouraged to attend monthly learning collaborative style implementation meetings held to highlight successes and address any challenges or concerns that have risen for facilitators during implementation processes. As this is an active implementation, sites are responsible for marketing and advertising. Per their grants, sites are able to provide meals, transportation, childcare, or incentives (e.g., gift cards, gas cards) for workshop participants. All marketing and promotional materials will be sent to the research team on a quarterly basis for examination in Aim 3 of the current study.

### 2.2. Participants

Eligibility criteria will require participants to be over the age of 18, English speaking (i.e., native or fluent), a Pennsylvania resident (verified by zip code), and a parent of at least one child under 13 years of age. Participants must also have internet access to complete the experimental procedures. For the purpose of this research, the term “parent” is loosely defined to include any primary caregiver of a child under 13-years old including, but not limited to, birth or biological parents, stepparents, foster parents, or grandparents. Screening for eligibility will be conducted through designated REDCap fields that ask participants to self-confirm that they meet criteria. Additional screening for bots (i.e., non-human respondents) will be conducted by the research team using “human” questions in Survey 0 (e.g., “Are you a human?”, “What color is a lemon?”) as well as a logic question (e.g., “Rachel thanked Matilda for all the help she received. Who received help?”). We use a ReCAPTCHA tool as recommended in the literature [28] and learning from prior our experience [24], our team has identified common patterns of bot entries (e.g., multiple sequential registrations within seconds of each other, participants with two first names, zip codes outside of the eligible area) and will be manually flagged by the research team for review.

### 2.3. Experimental procedures

All procedures were approved by the Institutional Review Boards at New York University and the Pennsylvania State University. A waiver of written consent was obtained wherein if participants decided to move forward in the survey after viewing the consent form, they were providing their implied consent. Study recruitment launched on May 1, 2024, and the targeted date for finalizing recruitment is December 31, 2024. As randomization at the site level is not feasible, parents who participate in the *Smarter Parents* workshop with one of our 9 partner sites will comprise the experimental group (target *n* = 206). Control participants (i.e., those who do not receive the *Smarter Parents* workshop; target *n* = 206) will be recruited from generalized recruitment ads distributed by community partners in Pennsylvania (not engaged in Project Safe and Smart) at similar agencies to those providing the workshop and recruiting the experimental group.

Participants, whether experimental or control, will complete three 15-minute surveys administered on REDCap (Research Electronic Data Capture) [29]: (a) Survey 0 (i.e., baseline), upon registration for the research; (b) Survey 1, completed 1-month after Survey 0 and workshop attendance, where applicable; and (c) Survey 2, 3-month follow-up (Fig 1). Participants will scan a QR code located on the recruitment materials to bring them to the screening form which then automatically proceeds to the consent form and will be provided a copy for download. Advancing to the first survey indicates their implied consent. Each subsequent survey will be sent at the appropriate timepoint via unique REDCap link to the email address the participant provides in Survey 0. Email reminders to complete each survey will be sent every two days up to a total of five times per participant.

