There is a paucity of standardized measures to demonstrate actual use of protective behaviors. We will leverage this study to pilot a questionnaire format for the Parents Use of Behavioral Strategies Interview (PUBSI), a project generated assessment tool, at Survey 2. The 23-item assessment will evaluate parent use of protective behaviors using mixed response types including: yes or no questions; a 5-point Likert scale assessing confidence; and short answer textboxes. Examples of questions include “Have you made changes to your home environment to protect your child from sexual abuse?”, “How confident are you that your child knows who to go to (or talk to) if they feel unsafe?”, and “What names does your family use to refer to private parts?”. Change in the prevalence of CSA is the ultimate outcome of interest; however, the stigma of and mean time to disclosure [32–34] reduce the feasibility of using administrative data for outcomes in any CSA intervention research. In addition, verifying self-report accuracy is beyond the scope of this study. The outcome of interest in the current study is the increased use of CSA-related knowledge and self-reported use of protective behaviors.

Participants in the experimental group will also be asked to complete a satisfaction form on Survey 1 (delivered 1-month post-workshop, Fig 1). This form asks the parents about their perceptions on preventing CSA before and after the workshop as well as the acceptability of the program and how likely they are to recommend the *Smarter Parents* workshop to other parents. To understand the ways in which parents interacted with the workshop, parents will be asked to report the device used to join the workshop (i.e., desktop computer, laptop, tablet, etc.). Parents will also be asked to provide suggestions on how to make the workshop more accessible to caregivers and how to promote the workshop in their community (e.g., fliers in school, school-based apps, counselor recommendations, etc.).

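### Survey 1 is timed from the workshop for experimental parents but from Survey 0 for controls, so the DID does not cancel a time trend over the registration-to-workshop lag

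*Protocol article*

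**What the plan says.** The protocol article fixes the timing in four places.

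- Baseline, both groups (section 2.3): "Survey 0 (i.e., baseline), upon registration for the research".
- Position of the workshop (abstract, Methods): experimental parents attend a "workshop between the Surveys 0 and 1".
- First follow-up (section 2.3): "Survey 1, completed 1-month after Survey 0 and workshop attendance, where applicable".
- First follow-up, experimental group (section 2.4): these parents complete "a satisfaction form on Survey 1 (delivered 1-month post-workshop, Fig 1").

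The last survey is described as "Survey 2, 3-month follow-up", with a pointer to Fig 1, which is not shown in the text available.

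The article treats research registration and workshop attendance as separate events. Section 2.5 makes the experimental group's first gift card conditional on both Survey 0 and verified attendance. Section 2.1 has facilitators report registrants and participants separately for each workshop. The article gives no upper limit on the time from Survey 0 to the workshop, and no matching date from which a control's surveys are counted.

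Section 2.6.2 bases the main comparison on DID, that is, on change over time in one group against change over time in the other.

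**The concern.** DID removes a time trend that the two groups share, provided that both groups' changes cover the same length of time. Here the experimental change runs over one month plus the wait for the workshop, and the control change over one month. Any movement in the outcome that would occur without the workshop has longer to act in the experimental group, and that surplus is counted as workshop effect. The parallel-trends assumption does not help: the trends can be exactly parallel and the surplus remains.

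The primary outcome is the 15-item ASK. One of the two items quoted in section 2.4 asks whether the parent has already talked with the child about self-protection from abuse, and agreement with it could plausibly rise as months pass. Section 2.6.1 plans for a small effect, d = 0.2, so a modest trend is not automatically negligible.

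**Working it through.** **Inputs from the article (section 2.6.1):** d = 0.2, pre-post correlation 0.7, α = 0.10, 158 per condition before attrition. **Assumed, because the article does not give them:** 80% power, two-sided testing, the lag L from Survey 0 to the workshop, and a drift δ in SD per month common to both groups.

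**Step 1: reproduce the plan's figure.** With a baseline-adjusted variance of 1 − 0.7² = 0.51, n = 2 × 0.51 × (1.645 + 0.842)² / 0.2² ≈ 158 per condition, or 316 in total against the stated 317. The timing point does not change this number; it only supplies the scale for what follows.

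**Step 2: read the timing rule.** A survey that is one month after Survey 0 and, for workshop attenders, also after the workshop is naturally one month after the later event. The intervals from Survey 0 to Survey 1 are then:

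- experimental: 1 + L months
- control: 1 month

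**Step 3: carry this into the DID.** With workshop effect τ:

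- experimental change = τ + δ(1 + L)
- control change = δ × 1
- DID = τ + δL

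The bias is δL. It is zero if either the lag or the drift is zero, and it is negative if drift is downward.

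**Step 4: illustrate the size.** Lag in months = weeks × 7 / 30.44. The type I error column takes 158 per condition and a change-score SD of √(2(1 − 0.7)) = 0.775, so SE = 0.775 × √(2/158) ≈ 0.087. It gives the probability of rejecting at a nominal two-sided 0.10 when τ = 0 and the estimate is shifted by δL. In the last three columns the first value is for δ = 0.02 and the second for δ = 0.05.

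| Assumed lag | Experimental interval (control = 1.00 month) | Bias, SD | Share of d = 0.2 | Type I error |
|---|---|---|---|---|
| 0 weeks | 1.00 | 0; 0 | 0%; 0% | 0.100; 0.100 |
| 1 week | 1.23 | 0.005; 0.011 | 2%; 6% | 0.100; 0.103 |
| 2 weeks | 1.46 | 0.009; 0.023 | 5%; 11% | 0.102; 0.112 |
| 4 weeks | 1.92 | 0.018; 0.046 | 9%; 23% | 0.108; 0.147 |
| 8 weeks | 2.84 | 0.037; 0.092 | 18%; 46% | 0.130; 0.281 |

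For example, at 4 weeks L = 28 / 30.44 = 0.92 months, and 0.05 × 0.92 = 0.046 SD, which is 0.046 / 0.2 = 23% of the planned effect.

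**Step 5: Survey 2.** If it is counted from the workshop for experimental parents and from Survey 0 for controls, the intervals are 3 + L against 3 months, and under linear drift the bias is again δL. If it is counted from Survey 0 in both groups, this bias is absent at Survey 2. The available text does not settle which applies.

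**The case against.** The strongest reply is that this may amount to very little. Parents reach Survey 0 through a QR code on recruitment material, and nothing shows how long before a workshop they do so; it could be days. No drift in ASK is documented either. At a 2-week lag the assumed drifts move the type I error only from 0.100 to between 0.102 and 0.112. Marked inflation needs a long lag together with the higher drift. All of this stands, and it limits what can be claimed about size.

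Four stronger readings are tempting, and the article does not support them.

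- **That sections 2.3 and 2.4 contradict each other.** A reader might infer that a survey cannot be one month after both Survey 0 and the workshop unless the two coincide. Read as one month after the later event, the sections agree. It is that consistent reading which produces the unequal intervals.
- **That the plan fails to define Survey 2.** The text sends the reader to Fig 1, which is not shown and may give the starting point.
- **That the ratio of intervals measures the bias.** An experimental interval 1.46 or 1.92 times the control interval follows only from an assumed lag, and it says nothing about distortion of ASK without a drift.
- **That ASK as a whole accumulates with time.** Only one quoted item has that character. The other quoted item is factual knowledge, and agreement ratings on a Likert scale can also fall.

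It can also be said that survey windows and date handling often sit in a full protocol or analysis plan. That is fair for windows and model terms. The point here rests on the timing rule that the article itself states.

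**Conclusion.** The point holds as a statement about design. As written, the baseline-to-Survey 1 interval is longer in the experimental group by the wait between Survey 0 and the workshop, and the DID estimate includes any common drift over that wait. The bias is drift × lag.

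Its size cannot be derived from the article. The figures in the table rest on an assumed linear drift, shared by both groups, of 0.02 to 0.05 SD per month, and on assumed lags. They do not show that the trial will be biased by that much. Nor does the article support saying that the bias must favour the workshop, since that depends on drift being upward. The correction is worth making because the planned effect is small and the remedy is cheap.

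**What to change.** Put both groups on the same elapsed-time clock, in one of two ways.

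1. Open Survey 0 only within a short fixed window before the workshop. The window caps the lag: at one week, the assumed drifts leave 0.005 to 0.011 SD.
2. Give each control an index date, using a lag drawn from the experimental group's observed Survey 0-to-workshop lags, and time the control's Surveys 1 and 2 from that date. Experimental Surveys 1 and 2 are timed from the workshop. This equalises elapsed time and keeps time since workshop constant for experimental parents.

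In either case, state the starting point of both follow-up surveys for each group in the text of section 2.3.

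For participants already enrolled, add a sensitivity analysis on actual survey and workshop dates. It should estimate drift from the controls' three surveys and adjust the experimental change for the extra time. It rests on the controls' trend between surveys applying to experimental parents. A single days-since-Survey-0 covariate should not be relied on: if controls are all surveyed at about one month, elapsed time is largely confounded with group. Workshop dates are already recorded on the implementation forms (section 2.1).

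The cost is a REDCap scheduling change and a minor IRB modification. Because recruitment opened on May 1, 2024, early and late enrollees would follow slightly different schedules, which should be reported and allowed for in the sensitivity analysis.
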